### 5.5 Educational performance

We argue for two types of rapport to be distinguished: productive and unproductive. Both types are associated with important health and wellbeing benefits, such as feelings of social cohesion. However, we define productive rapport as that which serves not only to improve wellbeing, but also to increase learning gains when two children collaborate. Unproductive rapport, on the other hand, may serve to distract the learners and reduce learning gains. To assess what behaviors identify productive rapport, we will assess the learning gains of the individuals in each dyad, and the mean learning gain of the dyad, each week and over the period of the 6 weeks, as follows: as described above, the children will individually report their hypotheses and evidence to a locally-located experimenter each week, after the collaborative and free discussion phases are finished. This “reporting out” serves as a metric of performance on each week's work. In addition, the delta between a pre-test (before the 6 weeks begin) and post-test (after the end of the 6^th^ week) will measure learning gains over the course of the 6 weeks for each individual and for the dyad in order to assess the relationship between IBS, use of conversational behaviors, level of rapport, and learning gains. The pre-test and post-test will be similar to the first task used in week 1 and 2, and they will be administered by the experimenter located in each venue. Here the experimenter will show the child an image of a new imaginary animal (a different animal for the pre-test than for the post-test), and several pictures of environments, and ask the child whether each of the environments would be a good or bad place for the animal to live in and why. After the child has given arguments for why each of the environments would be suitable or unsuitable for the imaginary creature, the experimenter will ask which of the environments would be best and why. Once again this will last no more than 8–10 min. The students' responses on the weekly read-out and the pre- and post-test will be annotated for instances of every-day science reasoning language (hypotheses, claims and evidence, expressed in lay language, such as “I *think that* he can climb trees *because* he has long claws”). The annotation will be carried out using a scoring manual for everyday science language that we developed for prior work (Finkelstein et al., 2013; Finkelstein, 2018), and that has achieved high inter-rater reliability. The manual was developed based on a significant body of prior work (*inter alia*, Lemke, 1990; Kafai and Ching, 2001; Kurth et al., 2002; Nemirovsky et al., 2004). The categories include “testing or evaluating ideas”, “causation”, “explanation”, sorting/classifying”, and “comparing”, among others. The children's interactions with one another, both during the collaboration phase and the social phase are also annotated for conversational behaviors and for rapport, as described below.

## 6 Data analysis

Intrinsic to the novel methodology we are proposing is the alignment of neural data with multimodal conversational data on the one hand, and ratings of interpersonal rapport on the other. Synchronization of the video, audio and fNIRS equipment will be carried out by event timings from PsychoPy (Peirce et al., 2019), as described above. For the analyses below, therefore, while potentially challenging due to the different time-scales of the different modalities, we use the mean calculated on each 30-second window for each data type, and can therefore synchronize the different behavior streams (audio, video, rapport estimations, and IBS) using the event codes recorded in the fNIRS data, prior to subsequent cross-data type analysis.

### 6.1 Claim 1: conjunctions of conversational behaviors across modalities better predict IBS

We argue that focusing on a single conversational behavior (such as eye gaze) under-estimates the complex interplay among modalities in their relationship to neural synchrony. To adduce evidence for this claim we will leverage Long Short-Term Memory (LSTM) networks to predict IBS on the basis of temporal sequences of behavioral data (see Table 1 for further details on the behavior types and variables). Since conversational behaviors are likely to lead to IBS with a certain lapse of time, we insert a 1 to 10 second time lag between the sequences of conversational behaviors and the IBS (Chang et al., 2022). The dataset will be structured into sequential behavioral data over time, each associated with a 30-second interval IBS value and normalized through a Min-Max scaling technique, ensuring consistent proportions across all features, while preserving the original distribution of the data.

**Table 1 T1:** Data sheet.

**Level of data type**	**Modality**	**Dyadic status**	**Specific variables**	**Notes**
Conversational Behavior	Verbal	Non-reciprocal	◾Self-disclosure	Number of behaviors per 30 second epoch.
			◾Reference to shared experience	
			◾Praise	
			◾Teasing	
		Reciprocal	◾Mutual self-disclosure	
			◾Mutual reference to shared experience	
			◾Mutual teasing	
	Paraverbal	Non-reciprocal	◾Pitch shift	
			◾Shift in speed of speaking	
			◾Shift in loudness	
		Reciprocal	◾Mutual pitch shift	
			◾Mutual shift in speech rate	
			◾Mutual shift in loudness	
	Nonverbal	Non-reciprocal	◾Smile	
			◾Head nod	
			◾Gaze at other person	
		Reciprocal	◾Mutual smile	
			◾Mutual head nod	
			◾Mutual eye gaze	
Rapport State		Rapport rating (1–7) for each 30 second interval for each dyad		
Educational Performance		Every week	Task 1–3, week (with x = 1–6)	◾Number of hypotheses per weekly 8–10 min read-out
				◾Number of pieces of evidence per 8–10 min weekly read-out
IBS				◾Right hemisphere ROIs

The study will employ a hierarchical LSTM model to process these multimodal inputs. Within this framework, different LSTM modules will be dedicated to distinct input modalities, with their outputs subsequently merged in the following stage. Given that each modality may generate inputs at varying frequencies, we will synchronize these signals, setting a uniform frequency for the temporal signals that aligns as a common multiple of their various frequencies. To overcome the inherent limitation of traditional LSTM models, which often lose track of initial inputs over time, we will incorporate attention mechanisms known for their effectiveness in preserving memory. Additionally, the LSTM model will feature a feed-forward network capped with a softmax function at its output, aiming to categorize the hidden representations into specific conversational behaviors. The model's weight functions will be honed through supervised learning, utilizing Back Propagation Through Time (Mozer, 1995). For the training of our LSTM model, we will employ cross-entropy loss as a key metric.

Training will involve temporal cross-validation, preserving the chronological order of sequences. Post-training, we will employ two techniques for feature importance analysis: an ablation analysis to selectively remove features in such a way as to evaluate their impact on model performance, and SHAP (SHapley Additive exPlanations), a model agnostic method proven effective in our prior work (Grimberg et al., 2022), for quantifying each feature's contribution to rapport predictions. The model's performance will be evaluated on a distinct test set, with adjustments made based on results. This comprehensive approach will allow us to not only predict IBS from behavioral data but also determine the contributions of specific behavioral features and combinations of features, shedding light on the factors influencing IBS dynamics.

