#### 5.2.2 Inter-brain synchrony

Inter-brain synchrony will be calculated using wavelet transform coherence (WTC), which allows comparison of similarity between signals in terms of spectral content (Czeszumski et al., 2020). WTC calculations will be conducted using the hyperscanning Python pipeline (HyPyP) developed by Ayrolles et al. (2021), across six regions of interest (left and right PFC, left and right TPJ, left, and right STS) within the low-frequency range 0.01 to 0.15 Hz. This range is chosen to filter out respiration and heart rate while still allowing a relatively wide range of frequencies implicated in free verbal interaction in prior work (specifically Mayseless et al., 2019; Nguyen et al., 2021b). Like these previous authors, however, we will carry out visual inspection and spectral analyses and add higher frequencies if motivated by the data.

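### Section 6.1 says the LSTM predicts inter-brain synchrony, but specifies an output, loss and SHAP target that do not fit it, and lets the model be adjusted on its test-set results

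*Protocol article*

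**What the plan says.** Section 6.1 opens with its aim: "we will leverage Long Short-Term Memory (LSTM) networks to predict IBS on the basis of temporal sequences of behavioral data". The behavioural sequences are "each associated with a 30-second interval IBS value and normalized through a Min-Max scaling technique". Section 5.2.2 gives the source of that value: "Inter-brain synchrony will be calculated using wavelet transform coherence (WTC"). Table 1 lists the verbal, paraverbal and nonverbal behaviours, counted per 30-second epoch; these are the model inputs.

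The model description that follows in 6.1 fixes these elements:

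- Output layer: a feed-forward network "capped with a softmax function at its output, aiming to categorize the hidden representations into specific conversational behaviors".
- Loss: cross-entropy.
- Explanation: an ablation analysis that removes features and looks at model performance, and SHAP to quantify each feature's "contribution to rapport predictions".
- Cross-validation: "Training will involve temporal cross-validation, preserving the chronological order of sequences".
- Final evaluation: performance "will be evaluated on a distinct test set, with adjustments made based on results".

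The section closes by repeating that the approach predicts IBS from behaviour and identifies which features, alone and in combination, contribute.

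**The concern.** Claim 1 is comparative: behaviours combined across modalities should predict IBS better than any single behaviour or modality. Testing it needs a held-out measure of IBS prediction error for each set of inputs. The output layer, the loss and the explained quantity in 6.1 do not supply one.

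Separately, a test set whose results lead to changes in the model stops being a test set. The performance finally reported would be partly selected on the data meant to verify it.

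This is the only analysis described for Claim 1. Section 7 intends the behaviours that look most effective in analysis to be implemented in the virtual peer, so an attribution to the wrong target could carry forward into that system.

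**Working it through.** **Part 1: what the model outputs.** There is no stated figure to reproduce, so the elements are set side by side.

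| Element | Where | What is specified | Fits a continuous IBS target? |
|---|---|---|---|
| Aim | 6.1, opening and close | IBS predicted from behaviours | Yes |
| Target value | 6.1 and 5.2.2 | One Min-Max scaled IBS value per 30 seconds, from wavelet coherence | Yes |
| Inputs | Table 1 | Conversational behaviours | Yes, as inputs |
| Output layer | 6.1 | Softmax over conversational behaviours | No: these are the inputs |
| Loss | 6.1 | Cross-entropy | Only if IBS is put into classes; none are defined |
| SHAP target | 6.1 | Rapport predictions | No: a third quantity |

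The softmax, the behaviour classes and the cross-entropy loss agree with one another as a behaviour classifier. They do not agree with the aim. Ablation measures loss of model performance, and the only performance the specified output and loss define is that of the classifier.

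**Part 2: adjusting on the test set.** The text gives one held-out set, evaluation on it, then adjustment. No further set is named. The article gives neither the number of variants nor the test share, so what follows is an illustration.

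Assumptions not in the document: K independent variants with no predictive skill; one independent value per test dyad; correlation r as the metric; n test dyads. The total of 176 dyads is from section 4.1.

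Under no skill, r has standard deviation 1/√(n − 1). The mean of the best of K is therefore about m(K)/√(n − 1), where m(K) is the expected maximum of K standard normals: 1.163, 1.539 and 1.867 for K = 5, 10 and 20.

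- n = 35 (20% of 176): √34 = 5.83, giving 0.20, 0.26 and 0.32.
- n = 176 (every dyad contributes test data): √175 = 13.23, giving 0.09, 0.12 and 0.14.

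Simulation (4,000 replicates per cell) agrees to within 0.01:

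| Test dyads | K = 5 | K = 10 | K = 20 |
|---|---|---|---|
| 18 (10%) | 0.28 | 0.37 | 0.44 |
| 35 (20%) | 0.20 | 0.26 | 0.32 |
| 53 (30%) | 0.16 | 0.21 | 0.26 |
| 176 (all) | 0.09 | 0.12 | 0.14 |

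The chance that at least one of K no-skill variants passes at 0.05 is 1 − 0.95^K: 22.6%, 40.1% and 64.2% for K = 5, 10 and 20.

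A lower bound comes from treating epochs as independent. Section 5.4 gives 192 to 240 dyadic epochs per dyad over six weeks, so 35 dyads give 35 × 192 = 6,720 to 35 × 240 = 8,400 test epochs. Then 1.163/√8,399 = 0.01 for K = 5 and 1.867/√6,719 = 0.02 for K = 20. Epochs within a dyad are correlated, so the true value lies above this, and one value per dyad is the pessimistic end.

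**The case against.** The strongest reply is that IBS is named as the target at both ends of the section, so the mismatched clauses are drafting slips. The reference to rapport sits beside a citation of the team's earlier work and may be a single wrong word. This stands in part: the declared aim is not in doubt, and the fault is an internal contradiction, not a change of aim. But the output layer, its classes and the loss form a consistent set that does not fit a continuous target. An analyst following them would build a different model. This is a rule stated wrongly, not a detail left to a fuller plan.

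A reader might go further and infer that Claim 1 cannot be tested. The document does not support that. Once IBS is the output, the planned ablation is a route to comparing single with combined modalities, and design, sample and data collection are unaffected.

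A reader might also infer that the same dyads appear in training and test data because sequences are kept in chronological order. The text applies that order to cross-validation during training and names a separate test set without saying how it is drawn. The split unit can be left to the full plan.

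A third tempting inference is that over-fitting favours the multimodal model. That is not shown: the illustration gives every variant equal null skill and compares no rich model with a simple one.

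Finally, the phrase about adjustments may be loose wording for tuning on a validation set. Read literally it uses up the test set, and no untouched set is named to replace it.

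**Conclusion.** The point holds as two faults in section 6.1. First, the stated target and the specified output, loss and SHAP target contradict each other; followed literally, no IBS error results on which the Claim 1 comparison could be made. This rests on the text alone and needs no assumption.

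Second, adjusting the model on its test-set results makes the reported performance optimistic. The direction is clear, but the size depends on the number of variants tried and the effective test sample, neither of which the document gives. Taking one value per dyad, the illustrations run from about 0.09 (best of 5, 176 dyads) to 0.44 (best of 20, 18 dyads) in apparent correlation. They fall to 0.01–0.02 if all epochs from 35 dyads were independent. None of these figures is a prediction for this study, and none measures the multimodal versus single-modality contrast itself.

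**What to change.** Reword section 6.1 as follows:

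1. Make IBS the model output with a matching loss: a linear output with squared error on the 30-second value, or predefined IBS classes if softmax and cross-entropy are kept.
2. Apply SHAP and the ablation analysis to IBS predictions.
3. Make all adjustments on training and validation folds only, preferably grouped by dyad.
4. Score the final multimodal model and the best single-modality model once on the untouched test set, and compare their held-out IBS error.

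The cost is a rewording of the section, slightly more computing, and reported performance that will look less favourable.

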In the neurosciences a considerable body of literature has focused on the cognitive roots and neural signatures of social interaction in adults, demonstrating, for instance, the complementary roles of the mentalizing system (MS) and the mirror neuron system (MNS) (Sperduti et al., 2014; Sadeghi et al., 2022) including during peer-learning (Clark and Dumas, 2015). Within these systems, several key regions emerge: the prefrontal cortex (PFC), the superior temporal sulcus (STS), and the temporo-parietal junction (TPJ) (Molapour et al., 2021). The PFC plays a key role in social decision-making and emotion regulation (Franklin et al., 2017), processes which allow individuals to engage in prosocial behaviors that may strengthen social bonds. The superior temporal sulcus (STS) region is well-known for its involvement in a wide array of processes required for social interaction, such as understanding another's actions and beliefs, language, face perception, and the interpretation of others' eye gaze (Carlin and Calder, 2013; Monticelli et al., 2021). Finally, the TPJ, with its involvement in theory of mind processes (Saxe and Kanwisher, 2003), plays a role in perspective-taking, fostering the ability to engage in the kind of cooperative interactions essential for forming meaningful social connections. Moreover, the TPJ has been recently demonstrated to serve as a hub between self- and other-related behavior at the sensorimotor level, and a key input to the PFC for a more representational level (Dumas et al., 2020). However, studies of the mentalizing process focus in large part on single individuals, adducing evidence for hypothesized prerequisites for social interaction, and not social interaction itself, as a process co-constructed in real time by two or more participants. There are now, however, relevant technologies to study actual social interaction, such as hyperscanning; that is, the simultaneous measure of brain activity of at least two individuals engaged in interaction (Montague et al., 2002). And there are now relevant techniques to analyze social interaction. These include dyadic data analysis (Kenny et al., 2006), analyses that take the dyad as the unit of analysis, and the coordination dynamics framework (Tognoli et al., 2020), that allows social dynamics to be understood at multiple levels of description. In fact, researchers have increasingly argued, not to discount the importance of social perceptual processes, but to also integrate phenomena that require looking at two or more interactants at a time. This argument has recently been made for cognitive science (Dingemanse et al., 2023; Hamilton and Holler, 2023). It was first made for neuroscience in a visionary article by Hari and Kujala (2009), reiterated by Dumas et al. (2010), and Schilbach et al. (2013), and it has been echoed repeatedly since then, including in a recent special issue (Schirmer et al., 2021). In each case, the authors call for studies that involve two or more people engaging in interaction with one another in real time, and they call for analyses that look at the dyad as the unit of analysis, as well as the role of the individual in the dyad.

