While we sometimes refer to feeling instantly “in sync” with somebody we have just met, for the most part rapport fundamentally has to do with the change of a relationship over time. In order to assess the changes in rapport over the course of the 6 weeks of the longitudinal experiment, we will rely on the concept of utopy (Sinha, 2016). Prior work has shown that statistical summaries such as a measure of central tendency or proportion of high and low ratings of rapport, collapse the temporal dimension and are not as robust as more stochastic-based models which capture the evolution of rapport over time (Sinha, 2016). We will thus fit a Markov chain of order 1 to the sequence of 16 to 20 rapport ratings for each session (8–10 min), the sequence of 32 to 40 rapport ratings over the two dyadic sessions (collaboration and open-ended chat) and the 192 to 240 rapport ratings for the two dyadic sessions over the entire 6 weeks, and use the resulting transition probability matrix to generate a measure of the “utopy,” or likelihood of the dyad being in a high-rapport state. This likelihood is calculated as the sum of each transition probability weighted by the distance of the transition (Sinha, 2016; Madaio et al., 2017b). This allows us to assess the temporal dynamics of rapport.

As described above, we will also ask children after each interaction to rate their preferred closeness and feelings of closeness to their partner.

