### 6.4 Claim 4: not all rapport is productive: adding in performance data

While rapport is often seen as beneficial in general, and in particular for collaborative tasks, its impact on task performance is not uniformly positive. To investigate this, we propose integrating performance data into our analysis of IBS, conversational behaviors, and rapport. Methodologically, we will first compute the specific performance metrics relevant to the tasks undertaken by dyads in our study, as described above. In order to associate these metrics to conversational behaviors, rapport level, and IBS, over time, we count the number of hypotheses, and evidence statements supporting those hypotheses, in the read-out session between the children and the experimenter for each week, and we associate these performance metrics to the rapport utopy score for that week, and the mean IBS score for the collaboration phase for that week. Our hypothesis is that while a moderate level of rapport is likely to be beneficial for performance, either too little or too much rapport might hinder task effectiveness. This could be due to an overemphasis on maintaining harmonious interactions at the expense of task focus, or conversely, insufficient rapport leading to poor collaboration. We therefore expect to find a non-linear relationship, potentially inverted U-shaped, between rapport levels and task performance. To test this hypothesis we will employ regression models, including quadratic regression, to test the hypothesized inverted U-shaped relationship. This will enable us to assess the impact of varying levels of rapport on performance metrics while controlling for other variables. Furthermore, we will conduct subgroup analyses to explore if this relationship varies across different dyads, tasks, levels of IBS or ages, or over the 6 weeks of the study. This could involve stratifying dyads based on one of these variables. By integrating performance data, we aim to provide a more nuanced understanding of the role of rapport in collaborative tasks. This kind of analysis may be supplemented by machine learning models such as random forests, where the model is trained on a portion of the data, with the random forests constructing multiple decision trees during the training, and outputting the mean prediction of these trees. In essence this enables the model to recognize complex patterns, such as how different variables interact to affect task performance, thus potentially uncovering intricate relationships such as the hypothesized non-linear relationship between conversational behavior, rapport, and task performance. Techniques of this sort, however, require a significant amount of data as, after training, the model is validated on a separate dataset to assess accuracy. If 176 dyads are collected, the amount of data could be sufficient. The results could have important implications for how rapport is fostered in team settings, particularly in educational and organizational contexts, where performance outcomes are critical. The insights gained from this analysis could contribute to a more comprehensive model of interpersonal dynamics, extending beyond the simple premise that more rapport is always more beneficial.

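### The Claim 1 model is split by time, and nothing keeps a dyad out of both training and evaluation data, so adding modalities can appear to predict IBS by identifying the dyad

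*Protocol article*

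**What the plan says.** Section 6.1 trains a hierarchical LSTM to predict IBS from behaviour sequences, "each associated with a 30-second interval IBS value and normalized through a Min-Max scaling technique". The predictors are the Table 1 behaviours ("Number of behaviors per 30 second epoch"). The splitting rule is: "Training will involve temporal cross-validation, preserving the chronological order of sequences". The modality question is then judged by SHAP and by "an ablation analysis to selectively remove features in such a way as to evaluate their impact on model performance". On final evaluation the section says: "The model's performance will be evaluated on a distinct test set, with adjustments made based on results".

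No section says that folds or the test set are formed by dyad. Section 5.4 shows how much repeated data each dyad supplies: "the 192 to 240 rapport ratings for the two dyadic sessions over the entire 6 weeks". Section 5.2.2 normalises social-phase IBS against the same dyad's solo phase, without saying whether these values enter the LSTM. Section 6.4 offers an optional random forest in which "the model is trained on a portion of the data" and validation uses a separate dataset, again of unstated unit.

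**The concern.** Dyads can differ persistently in how much they smile, gaze or shift pitch, and in their measured IBS level. The protocol itself expects such differences. Claim 6 predicts that reciprocal behaviour and IBS both rise with age, section 5.1 notes that head size affects which region an optode samples, and section 5.2 restricts IBS to the channels that pass quality control in both children. (A genuine age link would survive a split by dyad. It is cited only to show that between-dyad variance is expected.)

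When the same dyads are in training and validation folds, a flexible model can learn a dyad's behavioural profile and return that dyad's usual IBS. More features make the profile more distinctive, so the error does not cancel in the ablation but leans towards the larger feature set. That is the direction of Claim 1. Accuracy of this kind says nothing about whether behaviour and IBS move together, and it would not carry over to new children, whom the virtual peer of section 7 is meant to serve.

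**Working it through.** **1. Repeated data per dyad.** A phase of 8–10 min at two epochs per minute gives 16–20 epochs. Two dyadic phases give 32–40, and six weeks give 6 × 32 = 192 to 6 × 40 = 240, which matches section 5.4. IBS uses the same 30-second epochs (section 5.2.1). With 176 dyads that is 176 × 192 = 33,792 to 176 × 240 = 42,240 epochs, but only 176 independent units.

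**2. Predictors.** Table 1 lists verbal 4 + 3 = 7, paraverbal 3 + 3 = 6 and nonverbal 3 + 3 = 6, so 19 in all.

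**3. Null model.** For dyad d and epoch t:

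- IBS: y = √ρy · b_d + √(1−ρy) · e_dt
- behaviour k: x_k = √ρx · u_kd + √(1−ρx) · ε_kdt

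All terms are independent, so behaviour carries no information on IBS except which dyad it came from. The ICCs ρy and ρx are assumptions, since the protocol gives none. Data: 176 dyads × 6 weeks × 36 epochs, 8 replicates. Predictors are running session means of 6, 12 or 19 behaviours. The flexible model is ridge regression on random Fourier features. R² = 1 − Σ(y−ŷ)² / Σ(y−ȳ_train)². The time split trains on weeks 1–4 and tests on weeks 5–6. The dyad split trains on two thirds of dyads and tests on the rest.

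| ρy (IBS) | ρx (behaviour) | Time split, 6 → 12 → 19 | Dyad split, 6 → 12 → 19 |
|---|---|---|---|
| 0 | 0.3 | −0.005, −0.011, −0.013 | −0.009, −0.016, −0.021 |
| 0.1 | 0.3 | 0.024, 0.042, 0.051 | −0.032, −0.053, −0.054 |
| 0.3 | 0.1 | 0.021, 0.053, 0.073 | −0.060, −0.081, −0.108 |
| 0.3 | 0.3 | 0.083, 0.156, 0.181 | −0.104, −0.132, −0.156 |
| 0.5 | 0.3 | 0.158, 0.268, 0.319 | −0.175, −0.206, −0.175 |
| 0.3 | 0 | −0.018, −0.036, −0.046 | −0.019, −0.035, −0.049 |
| 0.3, IBS centred within dyad | 0.3 | −0.008, −0.012, −0.016 | −0.007, −0.013, −0.021 |

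In this null model, knowing the dyad perfectly would give R² of about ρy, so 0.181 at ρy = 0.3 is about 0.181/0.3 = 60% of what pure dyad recognition could yield. A plain linear ridge shows the same pattern on a smaller scale: 0.006, 0.016, 0.026 at ρy = ρx = 0.3.

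**4. Why modest epoch-level ICCs suffice here.** The simulation has no week-to-week drift, so a mean over 36 epochs is very stable. At ρx = 0.3 its dyad share is 0.3 / (0.3 + 0.7/36) = 0.94, and at ρx = 0.1 it is 0.1 / (0.1 + 0.9/36) = 0.80. Real drift would lower these shares and the false gain.

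**5. Check on weekly means.** A second null simulation (176 × 6 weekly means, kernel regression, 40 runs per setting, same time split) gave R² for 19 versus 1 feature of 0.07 vs 0.00 (behaviour ICC 0.5, IBS ICC 0.5), 0.05 vs 0.00 (0.7, 0.2) and 0.21 vs 0.00 (0.7, 0.5). At lower ICCs there was little or no excess. By dyad, R² was at or below 0. Making the mutual behaviours correlate with their individual counterparts shrinks the gain: with both ICCs 0.5 and training on weeks 1–3, R² for all 19 fell from 0.047 to 0.022. With correlated mutual behaviours and ICCs 0.7 and 0.5, R² for 1, 6 and 19 features was about 0.00, 0.01 and 0.07.

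**6. Does stated normalisation remove it?** After the solo-phase Z-score, a dyad's mean is (mean social − mean solo) / SD solo. This still varies between dyads unless all respond alike, so the interactive-phase level remains. Min-Max scaling over the pooled data leaves it too. Scaling within dyad might reduce it, but the scope is not stated.

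**The case against.** The strongest reply is that the document does not say dyads are shared. Chronological order is compatible with folds grouped by dyad, and the test set is described as distinct. If chronology meant calendar time, folds could even hold partly different dyads, since section 4.2 starts with 9–10-year-olds. An article may also leave fold construction to a fuller plan. This stands in part. A reader might infer that the same dyads certainly sit in the final evaluation data, and the document does not establish that. But the splitting rule is stated rather than left open, its ordinary meaning with repeated sessions is earlier against later epochs of the same dyads, and a test set whose results prompt adjustments is not a clean safeguard.

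A reader might also infer that Claim 1 would be declared under the null at some high rate. The documents do not support this: section 6.1 states no significance test for Claim 1, it describes a softmax output with cross-entropy loss rather than R² on a continuous outcome, no LSTM was run, and the gain vanishes if either ICC is zero.

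Nor does "analyses that take the dyad as the unit of analysis" in section 2 contradict the split. It describes a method in the literature review and is not a rule for folds. The random forest is optional and is validated on separate data, so it cannot be called faulty as written.

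Finally, predicting later sessions of known dyads is a legitimate longitudinal aim, and the virtual-peer study gives a later check. However, even for that aim, accuracy gained by recognising dyads is not evidence that conjunctions of behaviours predict IBS.

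**Conclusion.** The concern holds in conditional form and is worth acting on. The only stated split is chronological, nothing keeps a dyad's epochs on one side, and the unit of the test set is not given. The bias, where present, grows with the number of features and so favours Claim 1. Over the assumed ICCs the false R² under a time split ran from none (an ICC of zero, low ICCs on weekly means, or IBS centred within dyad) to about 0.3 (IBS ICC 0.5, behaviour ICC 0.3 at epoch level). It was never meaningfully positive under a split by dyad. These sizes rest on assumed ICCs, mostly independent features and stand-in models. They show mechanism and direction and do not forecast the LSTM's error. Confidence is medium because the true ICCs and the composition of the test set are unknown.

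**What to change.** Replace the splitting rule in section 6.1 with text to this effect: cross-validation folds and the final test set are formed by dyad, with all weeks, phases and epochs of a dyad kept together, stratified by age group and gender; chronological order is preserved within each dyad's sequence; ablation and SHAP are computed on held-out dyads; uncertainty in the multimodal-versus-unimodal difference is taken over dyads; tuning is confined to the training folds and the final test set is used once. If the optional random forest of section 6.4 is run, its validation data should likewise consist of separate dyads.

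The cost is a few sentences and a grouped splitter in the code, with no new data. Reported accuracy will probably be lower and somewhat more variable, because whole dyads are held out.
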